### Stress measures (secondary outcome)

We will measure salivary cortisol, perceived stress and anxiety. Stress alters the dynamics of the diurnal rhythm of cortisol secretion, and people who are chronically stressed exhibit lower morning and higher evening concentrations, yielding flattened slopes [19, 20, 47, 62–67]. Samples will be collected using the passive drool method [68] at waking, and 12-h after waking to permit calculation of time point concentrations and the slope of cortisol from waking to evening. The saliva collection kit contains collection supplies, a response sheet and reminder instructions. Participants will be reminded to take and freeze samples at designated times the day before their scheduled health appointment via StANDApp and/or text. Participants will also be reminded to bring kits to their appointment the next day [69, 70]. In the field, samples will be stored in a manual-defrost freezer and shipped on dry ice (once per measurement period) to Northwestern University’s Laboratory for Human Biology Research where they will be thawed, centrifuged and the supernatant aliquoted into replicate samples in smaller tubes and analyzed in duplicate. Low, medium, and high concentration controls will be prepared in at t = 0 for use throughout the study to monitor inter-assay variability. Cortisol will be measured using the Salimetrics ELISA kit as per manufacturer’s instructions [71].

We will also use two stress indicators via the survey, including: 1) Anxiety and Depression, measured via NIH’s Adult PROMIS-29 Profile v2.0 [72, 73]; and 2) the Perceived Stress Scale [74], comprising 10 items (e.g., feeling nervous) measured on Likert-type scale (0 = low, 40 = max stress). The perceived stress scale has been validated in multiple populations, and the face validity and scale content were ranked high with a Kaiser-Meyer-Olkin coefficient of 0.82 [75]. The scale’s internal consistency reliability was good in multiple languages and convergent validity was supported by expected relationships with other mental health measures, including anxiety and depression [76]. The PROMIS-29’s (our measures of anxiety and depressive symptoms) internal consistency for sub-domains has been shown to be high (Cronbach’s α > 0.88), with adequate structural validity for most domains (CFI > 0.95, RMSEA < 0.05) [77].

### Anthropometric and cardio-metabolic measures (downstream outcomes)

Cardio-metabolic outcomes will include body mass index (BMI), waist-to-hip ratio, blood pressure, glycated hemoglobin A1C (A1C) and C-reactive protein (CRP). Height will be measured twice using a stadiometer (SECA Corp). Weight will be measured twice using a scale with bioelectric impedance capability (Tanita TBF-300). Waist and hip measurements will be taken twice with a Gulick tape, according to World Health Organization (WHO) procedures [78] and the waist-to-hip ratio calculated. Systolic and diastolic blood pressures will be measured as markers of cardiovascular disease (CVD) risk using an automatic upper arm monitor (Omron HEM-711DLX), according to American College of Cardiology recommendations [79]. With the patient seated, two blood pressure measurements will be taken at 30 s intervals. The average of each set of measurements will be used for height, weight, waist and hip measurements and blood pressure. BMI will be calculated and expressed as kg/m^2^. A1C [8, 80] will be measured from blood samples collected from finger-tip sticks using portable analyzers and test strips (A1CNow^+^). Participants will be given these results immediately, including normal ranges and recommendations for consulting a physician.

CRP will be measured to indicate chronic inflammation [81–90], associated with obesity, Type 2 diabetes, cancer, and CVD [89, 91–94]. DBS samples will be collected on Whatman 903 Protein Saver Cards [95, 96] from finger sticks following collection of blood for the A1C analyses. DBS serves as the lowest risk, least invasive blood sampling technique [95]. Circulating levels of CRP in young, healthy adults average 0.8 mg/l. Chronic stress induces small changes in the range of 2–5 ng/l necessitating the use of high-sensitivity assays for CRP [90, 97]. Upon collection of DBS, samples will be transferred to Northwestern University’s Laboratory for Human Biology Research where CRP will be eluted from the DBS and assayed using a CRP assay previously validated in their laboratory for use with DBS [84, 97]. To reduce inter-assay variability and improve quality control, all samples will be stored with humidity sponges and oxygen absorbents and frozen (− 20 °C) until the final data collection year (2022) and then analyzed concurrently, with no expected degradation.

### Survey

Basic demographic data information (age, sex, ethnicity, employment, household composition, length of residence) will be collected at recruitment or when re-contacted at each timepoint. Then, each participant will complete a self-administered paper survey in the privacy of their own home to assess: income, perceptions of the neighborhood [98–102], disease and prescription medication history [103–106], diet [107, 108], perceived stress [74], anxiety and depression symptoms [72, 73] (discussed previously), nature-relatedness [109]; all which were considered potential correlates of device-based PA and stress. Questions about the perceptions of the social and environmental features of neighborhoods have been shown to have moderate to high agreement (rho range = 0.42–0.91) [99]. Family Life, Activity, Sun, Health, and Eating (FLASHE) questions related to diet were reviewed by the scientific experts for consistency with existing, validated measures [108]. The nature-relatedness scale (NR-6) has been shown to demonstrate good internal consistency, temporal stability, and predict happiness, environmental concern, and nature contact [109]. Measures that may serve as confounders include: 1) symptoms of acute illness or infection or prescription medication which could influence biomarker measures; 2) attitudes toward nature using the NR-6, because these may influence behaviors; and 3) perceived safety which may influence stress [110], PA [111, 112], and park usage [113].

### Park observations and imagery

The positive visual exposures of interest include the presence of people using the park, signage, mowing and other signs of care [114], diversity of plants and birds and greenness. Negative visual exposures include the presence of litter, arson, graffiti and broken windows of buildings along the park perimeter (called signs of disorder). We will employ two methods to obtain these data. First, Audubon volunteers will inventory plants in quadrants and count bird species using point counts less than three hours after sunrise, measuring species abundances [115, 116]. Volunteers will be trained by Audubon, and inter-observer reliability assessed by having two or more observers collect data simultaneously but independently [117]. Plant/bird species richness and biodiversity measurement will employ the well-established Shannon Diversity and Simpson Indexes [118, 119] and Evar Evenness Index [116]. Trained graduate students will also make observations of signs of care and the System for Observing Play and Recreation in Communities (SOPARC) [120]. SOPARC provides an assessment of park users’ PA levels, gender, activity types, and estimated age and ethnicity groupings as well as information on a park’s level of accessibility, usability, supervision, and organization with a high internal correlation between items (r = 0.75) [120], and exhibiting high inter-rater reliability (0.80–0.99) [117]. All nine parks, each of which consists of only one target area due their small size, will be observed twice over one day (9 am-2 pm) during randomly scheduled days without rain in summer months, by two raters. INT and CNT parks will be observed at the same time on different days for parallel observations. Signs of care involve observations (presence/absence) of manmade and natural items in a park and provides a categorical quality rating for each item, which is based on qualitative work in Detroit [114]. Second, we will measure visual greenness and negative visual exposures (signs of disorder) via 360^°^ images captured along each park perimeter, using a mounted camera (Samsung Gear 360). Images will be used to measure visual greenness, by quantifying pixels of greenery using methods we developed [121]. Images will also be used to assess negative exposures using Marco et al.’s neighbor disorder coding protocol [122], which has shown acceptable ICCs (0.41–0.60) for the mean level of subscales of physical disorder and decay and has also been validated (showing high correlations) with physical audits, police impressions, and neighborhood socioeconomic status. This virtual auditing approach has been validated across several samples [123, 124].

We will employ two weighting schemes to create individual-level visual exposures from the park measures. First, we will weight each exposure by the actual contact time spent within view of the park in the one-week observation time using the GPS data [59], as described previously. Second, we will calculate the percentage of the viewshed occupied by the park, as seen from the participant’s home by capturing a 360° image from the front door of the home location. We will then create weights using these measures, to be applied to each of the visual exposures above.

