### Physical activity (primary outcome) measured using accelerometry

PA and sedentary behavior are measured using the ActiGraph accelerometer (ActiGraph model GT3X; Pensacola, FL). The ActiGraph is a triaxial accelerometer that measures acceleration in three planes of motion. Accelerometers capture and filter acceleration signals that are digitized and recorded as count values that are stored in investigator-defined intervals. Raw data are stored and may also be used for analyses.

The accelerometers will be worn on an elastic waistband, placed at the right hip, for all waking hours over seven days at each of the study’s four measurement time points (all during the summer or early autumn). Data will be collected in raw mode (30 Hz) and aggregated to 1-min values for analyses. The primary outcome is total PA counts per week, which has been associated with cardio-metabolic outcomes and biomarkers [22]. Analyses will also include number of minutes spent at given PA intensity levels using cut-points of Freedson et al. (≥1952 cpm) for moderate-to-vigorous intensity PA and Matthews et al. (< 100 cpm) for sedentary behavior, with light PA as 100–1951 cpm [55, 56]. We will also explore PA intensity levels using vector magnitude cutpoints [57]. In addition, these measures will be stratified by whether the PA occurred in the study park, in any greenspace, or elsewhere (based on GPS data). This will provide an indication of the proportion of ‘green PA’ from total PA. Periods of 60 min or more of continuous zeroes are considered non-wear times and not included in the calculation of total wear time. To be included, we will require ≥4 days of PA data (wear time ≥ 8–10 h/day) per time point [58]. If high levels of missing data exist, imputation strategies will be utilized. PA data will be collected at the same time of year (summer months only) to account for seasonality.

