### Mobility and park contact measured using GPS data

GPS units (Canmore) will be worn for one week, on an elastic belt with an accelerometer. At the end of the week of observation, data will be downloaded. To calculate the amount of time spent in ‘green PA’, these data will be linked with accelerometer data using time. Accelerometer data are then restricted using a threshold for PA and lux (> 400). Speed is calculated and data are further restricted by excluding speeds >25kmph. This results in total green PA. We will also use GPS data to calculate the actual contact time spent within view of the park [59] and usage of park. To calculate time spent within view of park, we will create ‘viewsheds’ around each park to determine all possible viewpoints from which the park can be seen, accounting for obstacles such as buildings, as we have done previously [60, 61]. To calculate usage of park, all GPS points located within 10 m of the park boundaries will be compiled to calculate time spent in park.

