To address missingness in our response data, we will employ strategies for imputation [139]. The techniques described above allow missing at random (MAR). Inverse probability weighting [140] will be investigated to accommodate missing data patterns that are not MAR. To minimize bias in analysis, we will adjust for factors that may be unbalanced between groups and examine the robustness of our conclusions under deviations of model assumptions. Below, we outline specific analyses for each hypothesis to be tested.

#### Hypothesis 1

We will separately evaluate average activity counts/minute and average moderate-to-vigorous minutes over the one-week observation period for each of the data collection periods. The predictor of interest is binary: INT versus CNT.

#### Hypothesis 2

The primary outcome, ‘green PA’, will be average activity counts/minute and average moderate-to-vigorous minutes over the one-week observation period while in parks and greenspaces in Detroit, as a subset of all activity.

#### Hypothesis 3

We hypothesize there will be an association between PA and the visual and auditory exposures. Instead of a binary predictor of interest, we will use continuous predictors for visual and auditory park exposures. Interaction terms between positive and negative exposures will also be assessed, as evidence suggests that negative sounds deplete the restorative benefits of natural sounds, [141] and that parks are often dominated by noise [45, 142].

#### Hypothesis 4

Each stress outcome will be evaluated separately and treated continuously. We will also explore potential mediators (e.g., PA) by adding each to mixed models as fixed terms, and adjusted mediation and partial correlation coefficients explored. We will adjust for prescription medication history and symptoms of acute illness as potential confounders.

#### Hypothesis 5

We will assess relationships with each stress indicator, in turn.

#### Hypothesis 6

We hypothesize there will be an association between each stress indicator and these exposures.

#### Hypothesis 7

We will compare INT and CNT groups from baseline through three-years post-restoration for changes in CRP and A1C (continuously measured) between INT and CNT groups. We will also consider the inclusion of prescription medication history and symptoms of acute illness as potential confounders.

#### Hypothesis 8

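### Hypothesis 3: weighting visual park scores by GPS time in view puts the participant's own movement into the predictor of physical activity

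*Protocol article*

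**What the plan says.** The visual measures are taken at the park. They include desirable features such as greenness and signs of care, and undesirable ones: "Negative visual exposures include the presence of litter, arson, graffiti and broken windows of buildings along the park perimeter".

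The section Park observations and imagery turns these into individual-level exposures in two ways. One scheme reads: "we will weight each exposure by the actual contact time spent within view of the park in the one-week observation time using the GPS data". Under the second, "we will calculate the percentage of the viewshed occupied by the park", judged from an image taken at the participant's front door. The weights are "to be applied to each of the visual exposures above", so positive and negative features are treated alike. Neither scheme is given priority.

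On the device, the section Mobility and park contact states: "GPS units (Canmore) will be worn for one week, on an elastic belt with an accelerometer". The same belt and week therefore supply both the weight and the PA outcome.

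For Hypothesis 3, the Statistical analysis section says "we will use continuous predictors for visual and auditory park exposures" and plans interactions between positive and negative exposures. It does not name the PA metric. The accelerometry section says "The primary outcome is total PA counts per week", while the text for Hypothesis 1 says "We will separately evaluate average activity counts/minute and average moderate-to-vigorous minutes over the one-week observation period". The general model has random effects for clustering and serial correlation, group and time terms, and a measure of environmental exposure. No separate term for contact time is stated.

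**The concern.** Hypothesis 3 is a claim about quality: that what people see and hear affects how active they are. A predictor for that claim should vary because the surroundings vary. Under the first scheme it also varies because participants move differently, and the movement is recorded in the same week as the outcome.

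Walking near home can raise both activity counts and minutes in view of the park. Sitting on a porch that faces the park raises minutes in view and lowers average counts. In either case an association can arise with no contribution from the quality of the park. The Discussion presents individual-level exposure as an important strength of the study, so results of this kind are likely to be read as evidence about quality.

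**Working it through.** **1. Stated figures.** The plan gives no number on this point and none is disputed. The sample figures used below are consistent: 620 × 0.85 × 0.90 × 0.95 = 450.6, matching the target of 450 in nine parks.

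**2. Algebra, with no assumed numbers.** Let S(k,h,t) be the score for feature k in park h in year t, and M(i,t) the minutes in view for resident i. The plan assumes each person is exposed mainly to one park. The weighted exposure is

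X(k,i,t) = S(k,h,t) × M(i,t).

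For two features in the same park and year, X(litter)/X(greenness) = S(litter)/S(greenness), a constant. Among neighbours, all weighted exposures are multiples of the same minutes. The planned positive-by-negative interaction becomes S × S × M². Rescaling M per person does not change this. The home-view weight is also a common multiplier, but it is fixed by the house and not produced by that week's movement.

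**3. Illustrative simulation.** The documents give no distribution of contact time or of activity while in view, so every input here is an assumption:
- 450 people, 50 in each of nine parks, one occasion, 1,000 runs;
- litter score gamma (shape 4, scale 1) by park, with no effect on PA;
- wear time 14 h/day (SD 1.5) for seven days;
- share of time in view log-normal: median e^−3.5 = 3.0%, log-SD 0.8 in the first two scenarios; median e^−1.5 = 22%, log-SD 0.5 in the third;
- person-level variation in activity, log-SD 0.35;
- home-view share uniform from 0 to 0.3, unrelated to PA;
- ordinary linear regression of PA on litter × minutes, pooled over parks, two-sided 5% test (2.5% per side).

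| Counts/min in view vs elsewhere | PA metric | Falsely positive | Falsely negative | Home-view weight, any rejection | Product term, with score and minutes also in model |
|---|---|---|---|---|---|
| 800 vs 300 | total counts | 87.6% | 0.0% | 4.5% | 10.0% |
| 800 vs 300 | counts/min | 75.7% | 0.0% | 4.1% | 10.1% |
| 300 vs 300 | total counts | 8.7% | 0.5% | 3.6% | 5.3% |
| 300 vs 300 | counts/min | 2.6% | 1.5% | 4.2% | 4.5% |
| 150 vs 400 | total counts | 0.0% | 84.5% | 5.5% | 3.5% |
| 150 vs 400 | counts/min | 0.0% | 97.1% | 4.4% | 3.5% |

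Total rejection runs from 2.6 + 1.5 = 4.1% to 97.1%, and the sign follows where people are active. The home-view column is near 5% because that share was assumed independent of PA.

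**4. Check by hand under a different model.** Work within parks on the log scale, where the park score drops out and only contact time is tested against PA. Assume log-SDs of 0.8 for contact fraction, 0.2 for wear time and 0.4 for activity rate.
- Shared wear time only, total counts: r = 0.2² / √[(0.4² + 0.2²)(0.8² + 0.2²)] = 0.04 / √(0.20 × 0.68) = 0.108. With n = 450, z ≈ 0.108 × √448 / √(1 − 0.108²) ≈ 2.3, giving about 63% rejection.
- Counts/min, activity and contact fraction correlated 0.1: r = 0.1 × 0.4 × 0.8 / √(0.16 × 0.68) = 0.097, z ≈ 2.06, about 54% rejection. At −0.1 the rate is the same with the opposite sign. At zero correlation it is 5%.

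The wear-time effect on total counts is thus about 63% here against 8.7 + 0.5 = 9.2% in step 3. One reason is the assumed spread of wear time: 0.2 here, 1.5/14 = 0.11 there. Neither figure can be taken from the plan.

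**The case against.** The strongest defence is that the article says only that exposures will be weighted. Scaling, covariate form and priority between schemes commonly belong in an analysis plan that is not shown. The home-view weight is already planned and offers a built-in comparison, and capturing contact away from home is a deliberate aim. Much of this stands, and it limits the point. It does not remove it: use of that week's GPS contact time as the weight is stated, and the proportionality in step 2 survives any common rescaling.

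Several stronger readings might be inferred and are not supported:
- **Hypothesis 6 has the same fault.** Its outcomes are cortisol and survey scales, not belt data. Confounding through PA is possible there, but that is a different and weaker argument.
- **Auditory exposures are affected.** They are predicted by kriging, with no contact-time weight stated.
- **Litter will appear to raise PA.** The sign is not fixed. Participants live within 0.5 km and time in view can include quiet time at home, which would give a false negative association.
- **A particular false-positive rate applies.** The simulations use assumed inputs and simple regressions, not the planned mixed model. The within-park version contains no park quality at all.

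**Conclusion.** The point holds for Hypothesis 3, visual exposures, first weighting scheme only. There, the weighted product mixes a park score with the participant's own behaviour, measured by the same belt in the same week as PA. On its own it cannot be read as an effect of exposure quality, in either direction.

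The structural part rests only on the stated construction and on the plan's assumption of one main park per person. The size rests entirely on assumptions and ranges from about nominal to over 90% false rejection. The part due to shared wear time nearly disappears when PA is expressed as counts per minute; the part due to activity while in view does not.

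The comparisons of intervention and control neighbourhoods, and the sample size built on them, are untouched.

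**What to change.** In Park observations and imagery, and in the Hypothesis 3 paragraph of Statistical analysis, state for the first scheme that:
- contact is expressed as a share of valid GPS wear time;
- park score and contact time enter as separate terms beside their product;
- the PA metric is counts per minute, not total counts;
- any claim about quality rests on the park-score and product terms, together with agreement with the home-view weight;
- the GPS-weighted product on its own is labelled exploratory.

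All the data are already to be collected, so the cost is wording and some precision. The park score takes at most 9 × 4 = 36 park-year values, so information about quality is limited. Separate terms reduce the artifact but may not remove it: rejection was still about 10% when in-view time was active. That run used raw minutes; the wear-share form was not simulated.

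Two alternatives are less attractive. Restricting the outcome to PA out of view of the park builds in the opposite coupling, because summed activity out of view falls as time in view rises. Making the home-view weight the sole primary exposure is a debatable trade, since it ignores contact away from home and may be near zero for many houses.
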